### Study procedure

Participants will receive face-to-face or online one-day training intervention including six sessions, with follow-up assessment at 1 and 2 months after training. Before the training, participants will be selected for study eligibility according to the study’s inclusion and exclusion criteria. They will be evaluated by a research staff blinded to the intervention in each hospital. After the selection, participants will be assigned to one of the two groups and informed by message about their training (place and time). Groups of participants will receive training according to their random assignment group. There will be three assessment points for the intervention and control groups: (1) immediately post training, (2) one month post training, and (3) two months post training. Assessments will be undertaken remotely, with online instruments. An overview of the protocol procedure is provided in Figure 1.

**FIGURE 1 F1:**
[figure not shown]
Design and flow chart of participants through the trial.

### Randomization and allocation concealment

After the initial screening, 1,399 health care workers within 42 hospitals will be randomized in a ratio of 1:1 to either system based PFA training (intervention arm) or training as usual only (control arm). A random sequence created by the study statistician using varying block size (2 or 4) randomization technique. 21 hospitals will be allocated to the PFA system training group and 21 to the training as usual group by a senior administrator not involved in the study. Health care workers from each trial hospital will subsequently be assigned to either the control or intervention group along with their hospitals to avoid contamination. The number of participants for each trial cluster (hospital) will be approximately 33. The random allocation of the hospitals will be sent independently to the co-investigators’ email address. The email will not be sent to each study site until interventions are assigned.

### Blinding

Study participants are blinded while the trainers are not blinded, however the outcome assessors will not get involved in the training and are blinded to group assignment. The assessors and statisticians of the study will be blinded throughout the procedure and will not anticipate which arm the participants will be assigned. Outcome data provided to the statistician will be deidentified.

The key researcher (MP) will not have access to any identifiable data provided by health care workers participating in the RCT and the RCT dataset will be fully anonymized. Furthermore, the participating hospital’s identity, which could be used to identify health care workers, will also be fully anonymized.

### Interventions

The system based PFA Training model has six modules including core concepts, knowledge and practice. The training model has been incorporated into a National Emergency Assistance Work Guideline (in press) which has been adopted by National Health Commission of China to prepare the front-line non-specialist health workers in emergency settings. A pilot of the training intervention found it to be feasible for the paraprofessionals. The PFA training course was culturally tailored and localized based on a PFA ToT manual which included elements of mental health awareness alongside PFA training based on the Johns Hopkins University PFA guideline (9).

The PFA training program consists of one-day sessions comprising lectures, practice, and group discussions between lectures. All training sessions will be organized by a group of three trainers (from CADERM) who meet the following selection criteria: experience using psychological interventions, excellent teaching and communication skills, and willingness to conduct training of practitioners. They attended a 2-day face to face ‘train the trainer’ session delivered by a licensed psychiatrist from the Second Xiangya Hospital with over ten years of clinical psychological intervention practice. Additional training support for these trainers included 1. a teleconference facilitated by experts from Psychological Rescue Branch of CADERM to receive advice, support, and feedback on running participants’ training; 2. The licensed psychiatrists attend participants’ training sessions facilitated by the trainers to provide support and feedback monthly.

Participant training consists of PFA intervention knowledge, skills, and self-care. During the training, health care workers will learn skills and knowledge to (1) identify mental health need surging in emergencies (2) assess the psychological need, (3) refer to special care, and (4) self-evaluate and self-care. During the first four sessions, participants will be instructed in the basic concepts in psychological first aid and key principles, signs of stress and traumatic reactions, and key components of PFA. The participants will carry out group discussions around a case study in emergencies and disasters. During the last two sessions, participants will be instructed to practice a PFA intervention in an emergency. To ensure participants’ adherence, we assigned a facilitator to each training site to encourage them to practice and attend the discussions.

Because of its brevity and specificity to healthcare workers, the PFA training does not train the healthcare workers to identify mental disorders. Still, they will be able to refer to appropriate mental health services. Only about 20 min of the entire content is spent explaining differences between broad psychiatric groups, such as mood versus psychotic illnesses. Instead, participants are taught to assess for general signs that a person might be developing a mental health problem interfering with their usual activities. As such, no hypotheses about changes in participants’ rates of problem recognition are made.

## Training as usual

The participants in the control arm will receive usual training delivered from the same training staff. The materials are based on the Mental Health Gap Action Program (mhGAP) Intervention Guide (IG) in non-specialized health settings (10) and its efficacy was already well established in the literature (11).

## Acceptability and fidelity

### Pilot of PFA training

Between June and August 2022 we conducted a pilot study in the Second Xiangya Hospital, a tertiary hospital located in Changsha, the capital city of Hunan province. This hospital was not in the cluster study. The aim of this pilot study was to evaluate the acceptability of the PFA training. A convenience sample of non-specialist health care workers in the Second Xiangya Hospital (*N* = 18) participated in PFA training based on a professional continuing education one-day format. Acceptability was measured by health care workers-perceived ease of use, importance, and intention for follow up.

Most participants were satisfied with the training given by the trainers (55.6% strongly agree), the structure and content of training (66.7% agree and 33.3% strongly agree) and had no problems in participating the on-line training sessions (55.6% agree and 27.8% strongly agree). Furthermore, most of the participants agreed that their participation in the PFA training was voluntary (50% agree and 50% strongly agree).

Overall, participants were either satisfied (55.6%) or extremely satisfied (44.4%) with the training program, with all providing positive feedback about the pilot intervention: “It helped me cope the emergency situations of my daily work. I felt stronger and more confident to provide emergency mental health service for the patients.” None of the participants thought that the training program had negatively affected them. Cronbach’s Alpha for the 10-items was high (α = 0.881) indicating strong internal reliability of the questionnaire. Participants completed the questionnaire after they had successfully passed a practical assessment of their PFA skills given by the course trainer.

### Fidelity of intervention training

Quality and fidelity are required for ensure the successful delivery of training interventionto the participants as planned (15). Fidelity will be checked in both groups. The train the trainer sessions took place in person before the trainee participants were enrolled. Interventionists (trainers) were given standardized manuals that contained the same information about the PFA theoretical foundations. Three trainers and eight facilitators were trained by one supervisor, a senior clinical psychiatrist with over ten years of experience. The training focused on promoting consistency and reliability across all the delivery sites with specific attention to the scripts and standardized content. During the implementation of the training interventions, supervision occurs at weekly intervals for trainers. Initial training sessions will be recorded for use in monitoring fidelity in both groups. See Tables 1, 2.

**TABLE 1 T1:** Fidelity checklist (Intervention arm).

Dimensions	Attributes of good practice	Questions for critical appraisal
I1: Statement of foundations	There should be a clear statement of the key concepts and principles of PFA The objective of the course should be defined The primary recipients of PFA should be stated clearly	Is there a clear statement of the key concepts and principles of PFA? Is the objective of the course specified and consistent with the stated concepts and principles of PFA?
I2: Statement of application/perspective	The primary recipients of PFA should be stated clearly The application of the training (conditions and timing) should be stated clearly and the application should be consistent with the stated principles and overall objective of the training The application of PFA should be specified and justified The outcome of the training should reflect the application/perspective of PFA and should be consistent with the objective of the training	Are the primary recipients specified? Is the application of the training consistent with the stated principles? Has the application of the training been stated and justified? Are the outcomes of the training consistent with the perspective, application and overall objective of PFA?
I3: Rational for the structure	The structure of the training should be consistent with a coherent theory of the PFA, and the crucial steps should be followed to implement the process of PFA intervention in disasters and emergencies All sources of evidence used to develop and inform the structure of the training (psychological first aid theory) should be described. The structure should be consistent with the objective of the training.	Has the evidence regarding the training structure been described? Is the structure of the training consistent with a coherent theory of PFA intervention in disasters and emergencies? Have any competing theories regarding PFA structure been considered? Are the sources of evidence used to develop the structure of the training specified?
I4: Strategies/techniques	There should be a clear definition of the strategies in PFA	Is there a clear definition of the strategies of PFA? Have all feasible and practical options been introduced? Is there justification for the exclusion of feasible options?
Safety and Comfort Stabilization Information Gathering: Current Needs and Concerns	The key strategies incorporated in the training should be described and the source of references should be given in detail to allow the trainees to be aware of the strategies that have been incorporated	Is the strategies incorporated into the model appropriate? Is the source for the strategies referenced? Are the methods for the strategies justified? Have the strategies incorporated into the training been described and referenced in sufficient detail?
Taking care of yourself	Individual self-care Reflect on own practice Protect yourself	Is the process of self-evaluation and self-caring clearly described? Have the method and resource been described in sufficient detail?
Practical Assistance Transfer and linkage with collaborative services	To offer practical help to survivors in addressing immediate needs and concerns	Is the logic of the PFA practice has been explained and justified?
	To link survivors with available services needed at the present time or in the future.	Have any differences between PFA and other interventions been explained?

**TABLE 2 T2:** Fidelity checklist (Control arm).

Dimensions	Attributes of good practice	Questions for critical appraisal
C1: Statement of foundations	There should be a clear statement of the key concepts and principles of the general mental health training	Is there a clear statement of the mental health concepts and training content?
C2: Statement of application/perspective	The application of the common psychological treatment and mental health interventions (conditions and timing) should be stated clearly and the application should be consistent with the stated principles and overall objective of the training	Are the primary recipients specified? Is the application of the training consistent with the stated principles? Has the application of the training been stated and justified? Are the outcomes of the training consistent with the perspective, application and overall objective of training?
C3: Rational for the structure	The structure of the training should be consistent with a coherent theory of the mhGAP, and the guideline should be followed to implement the interventions The structure should be dictated by current patterns of service provision All sources of evidence used to develop and inform the structure of the training (i.e., the theory of behavior based treatment) should be described. The structure should be consistent with the objective of the training.	Has the evidence regarding the training structure been described? Is the structure of the training consistent with a coherent theory of psychological therapy and mental health interventions in disasters and emergencies? Are the sources of evidence used to develop the structure of the training specified?
C4: Strategies/techniques	The training should include possible options that represent current good practice Trauma rehabilitation interventions in disasters and conflicts Psychological debriefing or critical incident stress debriefing (CISD)	Are there clear definitions of incorporated techniques? Have all feasible and practical options been introduced? Is there justification for the exclusion of feasible options?
Balint groups for medical practitioners	To help medical practitioners to reflect their practice and reconsider the emotional relationship with the patients	Have the Balint group process and techniques been described and referenced in sufficient detail?

Outcomes.

### Primary outcome

#### PFA knowledge, skills, and attitude

The primary outcome of the training is to facilitate non-specialist health care workers with the necessary knowledge, skills, and motivations to recognize a mental disorder presented in a vignette using the SKA-CPFA developed by licensed psychologists from CADERM (16). Post-test questions for PFA knowledge and skills in Chinese are also provided. Professional attitude will be assessed with a 20-item questionnaire with a score from one to five. Items are scored on a 5-point scale (1 = strongly agree; 5 = strongly disagree), and the total score ranges from 20 to 100. The higher the score, the more positive the gained capacity. The items are characterized in three domains: 1. how well the participants communicate their understanding of knowledge of PFA content (40 points); 2. skills related to the psychological intervention (including self-efficacy, proficiency, and self-assessment of relevant skills for the implementation of PFA) (30 points); 3. Attitudes including perception of barriers and personal judgments about the value of emergency psychological intervention (30 points). The questions reflect the health care worker’s non-judgmental attitude toward providing mental health support to other people. Responses are close-ended, and the resulting data will be recorded by a researcher blind to the cluster allocation and in accordance with the protocol.

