### Analysis

#### Data analysis

Statistical analysis will be performed using STATA (version 17 or later) and a *p*-value < 0.05 (two-tailed) will be taken to indicate statistical significance.

All trial participants who were randomly assigned at the start of the trial will stay in the sample for analysis under the intention-to-treat principle. It will be decided whether the intervention program is effective using random effect mixed modeling described below. Demographic factors will be evaluated for their potential influence on primary and secondary outcomes, and in cases where they do, they will be used as covariates.

The primary outcome for the statistical analysis will be the mean change in PFA-SKA score after 2 months of follow-up compared between intervention and control arms. The analysis allowed for this clustering in order to obtain unbiased estimation of the treatment effect and its standard error (SE). A two-level hierarchical mixed-effects model will be used to be fitted in the statistical analysis plan.

All secondary outcomes will be summarized by trial allocation group and follow-up period using mean, SDs and 95% CIs for the variables (ProQOL, GSE, PTGI scores). Statistical tests of differences for secondary outcomes will be performed using the same hierarchical mixed-effects model as the primary outcome analysis. In addition, participant-scores are also compared as change from post-training to 2-month follow-up using independent group t-tests.

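### The primary scale's response anchors run against its higher-is-better rule for any favourably worded item, so literal scoring would dilute, cancel or reverse the arm difference, depending on item wording not shown

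*Protocol article*

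**What the plan says.** All the scoring rules stand in one paragraph of the protocol article, under Primary outcome (PFA knowledge, skills, and attitude).

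- **Instrument:** "Professional attitude will be assessed with a 20-item questionnaire with a score from one to five".
- **Anchors:** "Items are scored on a 5-point scale (1 = strongly agree; 5 = strongly disagree".
- **Range:** the item scores are summed, with a minimum of 20 and a maximum of 100.
- **Direction:** "The higher the score, the more positive the gained capacity".
- **Domains of the same items:** knowledge, "how well the participants communicate their understanding of knowledge of PFA content (40 points"; skills, "including self-efficacy, proficiency, and self-assessment of relevant skills for the implementation of PFA) (30 points"; and "Attitudes including perception of barriers and personal judgments about the value of emergency psychological intervention (30 points".

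The paragraph also mentions a vignette and separate post-test questions on PFA knowledge and skills. It says nothing about recoding items.

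The Data analysis section then names the endpoint: "The primary outcome for the statistical analysis will be the mean change in PFA-SKA score after 2 months of follow-up compared between intervention and control". It does not say which components make up that score. The Hypothesis section expects greater improvement in the intervention arm. The Within-trial cost-effectiveness analysis section divides the cost difference by the difference in benefit, expressed as improvement in skills and knowledge.

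**The concern.** With these anchors, a participant who strongly agrees with a favourable statement, for example that they feel able to deliver PFA, scores 1 on that item, the lowest value. Someone who strongly disagrees scores 5. The total is nevertheless read as more capacity when it is higher. The two statements agree only if every item is worded unfavourably, or if favourable items are recoded before summing. The article states neither.

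The domain descriptions make wholly unfavourable wording implausible. Agreement with statements of self-efficacy, self-assessed skill or the value of the intervention would normally be favourable. Agreement about perceived barriers would normally be unfavourable. A mixed scale is therefore likely, and it needs a recoding rule.

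The superiority hypothesis and the ICER both depend on sign. If the direction of scoring were settled only after the arm difference had been seen, that would be a data-dependent change to the primary outcome.

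A second ambiguity lies in the same paragraph. The 20 items are introduced as an attitude questionnaire and then divided among knowledge, skills and attitudes, so it is unclear what the primary score contains.

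**Working it through.** **1. Reproduce the stated range.** 20 items × 1 = 20 and 20 × 5 = 100, so the total is a plain sum of items scored 1 to 5. The domain maxima give 40 + 30 + 30 = 100. At 5 points per item that is 8 + 6 + 6 = 20 items. The three domains therefore use all 20 items, and attitude accounts for only six of the items introduced under the attitude label.

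**2. Extremes under the stated anchors.** If all 20 items were favourably worded, strong agreement throughout would total 20 × 1 = 20, the worst score. Strong disagreement throughout would total 20 × 5 = 100, the best.

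**3. Effect on the score-point difference.** Let p be the share of items that are favourably worded and not recoded, and assume the same true gain g on every item. The shift in the total is

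g × [20(1 − p) − 20p] = 20g × (1 − 2p).

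| p | Items unreversed | Multiplier on score points |
|---|---|---|
| 0 | 0 | 1 |
| 0.25 | 5 | 0.5 |
| 0.5 | 10 | 0 |
| 0.75 | 15 | −0.5 |
| 1 | 20 | −1 |

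If the ICER denominator is this score, the cost per point doubles at p = 0.25 (1/0.5 = 2). The ratio has no finite value at p = 0.5, and its sign flips above that.

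**4. Effect on the standardised difference.** Leaving some positively correlated items unreversed also shrinks the SD of the total, so d is not simply multiplied by (1 − 2p). With k = 20 items of unit variance and common correlation r (before the sign error):

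- Variance, all items aligned: k + k(k − 1)r.
- Variance, share p unreversed: k(1 − r) + r[k(1 − 2p)]².
- d ratio: (1 − 2p) × √(first variance / second variance).

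The article gives no alpha for this scale; the 0.881 in the pilot section belongs to a 10-item acceptability questionnaire. Taking alpha = 0.88 as an assumption, r = 0.88 / (20 − 0.88 × 19) = 0.88 / 3.28 ≈ 0.27. At p = 0.25:

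- First variance ≈ 122; second variance ≈ 41.5.
- Ratio = 0.5 × √(122 / 41.5) ≈ 0.86.
- d ≈ 0.86 × 0.43 ≈ 0.37.

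The range over r at p = 0.25 is as follows. Uncorrelated items (r = 0) give 0.5 × √(20/20) = 0.5, so d = 0.215. Perfectly correlated items (r = 1) give 0.5 × √(400/100) = 1, so d = 0.43.

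**5. Effect on power.** The inputs from the Sample size section are d = 0.43, ICC 0.2, and 21 clusters of 30 per arm; alpha is 0.05, two-sided. The design effect is 1 + 29 × 0.2 = 6.8. The standard error of d is √(2 × 6.8 / 630) ≈ 0.147, with 2 × (21 − 1) = 40 degrees of freedom.

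| p | d (alpha 0.88 assumed) | Probability significant for intervention | Probability significant for control |
|---|---|---|---|
| 0 | 0.43 | 0.815 | about 0 |
| 0.25 | 0.37 | 0.69 | about 0 |
| 0.5 | 0 | 0.025 | 0.025 |
| 0.75 | −0.37 | about 0 | 0.69 |
| 1 | −0.43 | about 0 | 0.815 |

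The rows for p = 0.5 and p = 1 do not depend on the assumed alpha.

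**The case against.** The strongest reply has four parts.

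- **The items are not shown.** The conflict bites only where agreement is favourable and nothing is recoded. The instrument is cited to a source that may contain a recoding key, and a condensed article commonly leaves such a key elsewhere. This stands as a limit: p could be anywhere from 0 to 1, and the printed anchors may be a slip. But the point is not a missing detail. The article chose to state the anchors, the range and the direction, and they disagree for any favourable item.
- **The direction is already fixed.** Since higher is declared better, a reversed total would breach the article's own rule. That is true, but the rule does not cure anchors that run the other way. It only shows that the two sentences cannot both be applied to a favourable item.
- **The remedy is light.** Item responses can be rescored, and under complete reversal the two-sided test gives the same significance level with the opposite sign. Design and sample size are unaffected. All of this stands. It makes the correction cheap but does not make the stated rule safe to follow.
- **The make-up of the score is open.** The 40/30/30 split fits the 20-item total, but the vignette and the post-test questions might also contribute. This stands, so the choice belongs to the sponsor.

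A reader might infer that the trial's result will be reversed. The article does not support that without the item wording. A reader might also apply the multiplier to d and report 0.5 × 0.43 = 0.215 at p = 0.25. That holds only for uncorrelated items, which is implausible for a summed scale.

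**Conclusion.** The concern holds as a conflict in the stated scoring of the primary outcome. Followed literally, the anchors contradict the declared direction for every favourably worded item, and the described domains make it unlikely that there are none. The consequence ranges from no effect (p = 0), through cancellation (p = 0.5), to full reversal (p = 1). The score-point multiplier (1 − 2p) assumes equal gain per item. The d of about 0.37 and power of about 0.69 at p = 0.25 also assume an alpha of 0.88, equal inter-item correlations and an unchanged ICC. Which case applies cannot be settled from the article, and a simple reversed-anchor slip is a live explanation. Correction is still needed before scoring, because the sign of the primary comparison, and of any ICER built on this score, depends on it.

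**What to change.** 1. Make the scored direction match higher-is-better for every item. Either correct the anchors to 1 = strongly disagree and 5 = strongly agree, or keep them and score favourable items as 6 minus the response. Under either choice, list the items that are recoded; on a mixed scale there will be some.
2. Fix the scoring code before unblinding.
3. Reconcile the attitude label with the 40/30/30 knowledge, skills and attitude split of the same 20 items.
4. Have the sponsor state whether the PFA-SKA score in the Data analysis section is this 20-item total or also includes the post-test questions.

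The cost is one paragraph and a scoring script. No new data are needed, and the sample size does not change.
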